**Fig. 2 Fig2:**
[figure not shown]
Example of BPMDL-ICU. BPMDL-ICU = best possible ICU medication discharge list. N.B. This is a fictitious example, patient and doctor names are imaginary

In Erasmus MC, the pharmacist pre-registers the BPMDL-ICU in the CPOE/CDS system, so the ward doctor merely has to authorize this pre-registered medication list. Since pre-registration is not possible in the CPOE/CDS system of Haga Teaching Hospital, here the medication on admission is registered in the outpatient CPOE/CDS system, from where the ward doctor can easily transcribe this medication list to the inpatient CPOE/CDS system.

The study procedures are summarized in Fig. 3.

**Fig. 3 Fig3:**
[figure not shown]
Study procedure pre- and post-intervention. BPMDL-ICU = best possible ICU medication discharge list, BPMH = best possible medication history, BPML-GW24 = best possible general ward medication list 24 h after ICU discharge, CPOE/CDS system = computerized physician order entry systems with clinical decision support, ER = emergency room, HIS = hospital information system, ICU = intensive care unit, OR = operating room, PDMS = patient data monitoring system, TIM = Transfer ICU and Medication reconciliation program

### The gold standard medication lists

In order to detect MTEs, we defined a gold standard against which the actual prescribed medications are compared.

#### ICU admission

The gold standard is defined as the Best Possible Medication History (BPMH), which includes name, dosage, frequency, and route of all medication taken by a particular patient. The BPMH is created as follows: a pre-admission medication list is collected from the community pharmacy, which is combined with other available information about the patient’s medication, such as a letter from the Emergency department (if applicable), medication used in the general ward or medication lists from the operating room (OR) (if applicable). This medication list is verified by means of an interview with the patient and/or a relative, which will result in a BPMH.

#### ICU discharge

The gold standard is defined as the Best Possible General Ward Medication List 24 h after the ICU discharge (BPML-GW24). The BPML-GW24 includes name, dosage, frequency, and route of all medication that should ideally be prescribed within 24 h after ICU discharge. This list is based on the BPMH, on information found in the PDMS or the HIS of the ICU, on medication prescribed in the CPOE/CDS and, whenever necessary, on interviewing the ward doctor afterwards.

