#### Post-intervention phase

The pharmacist generates a BPMH for patients newly admitted to the ICU and the Best Possible ICU Medication Discharge List (BPMDL-ICU) for patients planned to be discharged. One day past ICU discharge, a medication chart of current medication in the CPOE/CDS will be printed and a BPML-GW24 will be compiled.

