### Outcome measures

Figure 1 presents a summary of outcome measures.

The primary outcome measures of this study are the proportion of patients with one or more MTEs at admission to the ICU and the proportion of patients with one or more MTEs after discharge from the ICU.

An MTE at admission is defined as an unintentional discrepancy between BPMH and medication prescribed within 24 h after admission to the ICU.

An MTE at discharge is defined as an unintentional discrepancy between the BPML-GW24 and the medication chart of the patient within 24 h after discharge.

Whether a discrepancy at admission is unintentional or not is based on information documented in the PDMS, the ICU standards of care and the ICU pharmacist’s interpretation of the situation (see Fig. 4 for the assessment of unintended medication discrepancies).

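### The discharge gold standard draws on the same ward prescribing system it is used to test, and pre-registration at Erasmus MC adds a risk, of unknown size, that errors are under-detected in the post phase only

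*Protocol article*

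**What the plan says.** Under the gold standard for ICU discharge, the BPML-GW24 is meant to hold "all medication that should ideally be prescribed within 24 h after ICU discharge". Its sources are the best possible medication history (BPMH), then "on information found in the PDMS or the HIS of the ICU, on medication prescribed in the CPOE/CDS and, whenever necessary", an interview with the ward doctor.

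Under Outcome measures, a discharge medication transfer error (MTE) is an "unintentional discrepancy between the BPML-GW24 and the medication chart of the patient within 24 h after discharge". The proportion of patients with at least one such error is one of the two primary outcomes.

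Under Collection of medication lists, post-intervention phase, one day after discharge "a medication chart of current medication in the CPOE/CDS will be printed and a BPML-GW24 will be compiled".

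The two phases fill the ward chart differently:

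- **Usual care:** the ward doctor transcribes orders from the ICU discharge letter.
- **TIM, Erasmus MC:** "the pharmacist pre-registers the BPMDL-ICU in the CPOE/CDS system, so the ward doctor merely has to authorize this pre-registered medication list".
- **TIM, Haga:** pre-registration in the inpatient system is not possible. The list goes into the outpatient system, and the ward doctor transcribes it from there.

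**The concern.** A gold standard can expose an error only if it was formed without relying on the thing being judged. Here the system that supplies the tested chart is also a named source of the reference. A wrong order on the chart can be accepted into the reference, and the comparison then shows no difference. This is incorporation bias in the measurement of a primary outcome.

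The second issue is asymmetry between the phases. At Erasmus MC after implementation, the chart is pre-filled with the list the TIM pharmacist prepared (BPMDL-ICU). If that list is wrong and the reference accepts the chart entry, the pharmacist's error sits on both sides of the comparison and is not counted. This route does not exist in the pre phase. A lower post-phase error rate could then partly reflect agreement of the intervention's own list with itself, and adjusting for patient characteristics would not remove that.

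**Working it through.** **Step 1. The reference and the tested object, side by side.**

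| | Source stated in the article |
|---|---|
| Reference (BPML-GW24) | BPMH; ICU PDMS/HIS; CPOE/CDS prescriptions; ward doctor when needed |
| Tested object | CPOE/CDS medication chart, within 24 h after discharge |

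The CPOE/CDS appears in both rows. The source rule is not phase-specific, so the overlap applies before and after. The article states no order of work that would have the reference finished before the chart is seen.

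**Step 2. The plan's own figures.** The inputs are 30% versus 15%, alpha 0.05 and power 0.80. The two-sided formula with continuity correction gives 134 per phase (stated: 133). Without the correction it gives 121. Allowing for 35% mortality, 133/0.65 = 204.6, so 205, as stated.

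Expected survivors per phase over 14 weeks, from the Sample size section:

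- Haga: 1500/52 × 0.70 × 0.65 = 13.125 per week, × 14 = 183.75
- Erasmus MC: 1800/52 × 0.70 × 0.65 = 15.75 per week, × 14 = 220.5
- Total 404.25; × 0.65 alive at discharge = 262.8, so 263

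Erasmus MC weight: 1800/3300 = 0.545.

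**Step 3. Equal masking in both phases.** Let s be the share of affected patients still detected. The observed RR is (0.15·s)/(0.30·s) = 0.50 for any s, so there is no bias. Power (pooled-variance normal approximation, no continuity correction) falls as follows:

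| s | Observed risks | Power, n = 133 | Power, n = 263 |
|---|---|---|---|
| 1.0 | 30% v 15% | 84% | 99% |
| 0.8 | 24% v 12% | 72% | 95% |

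**Step 4. Extra masking in the post phase, Erasmus MC only.** Assume no true effect, a true risk of 30% at both sites, full detection in the pre phase and at Haga, and a share h of affected post-phase patients at Erasmus MC hidden. The shares h are assumptions.

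Observed post-phase risk: p₂ = 0.30 × (1 − 0.545·h). RR = p₂/0.30.

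P(significant, favouring TIM) = Φ[(d − 1.96·se₀)/se₁], where d = 0.30 − p₂, se₀ = √(2·p̄(1−p̄)/n), p̄ is the mean of the two risks, and se₁ = √{[0.30·0.70 + p₂(1−p₂)]/n}.

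For h = 0.20 and n = 263: p₂ = 0.2673, d = 0.0327, se₀ = 0.0393, se₁ = 0.0393. Then (0.0327 − 0.0770)/0.0393 = −1.13, and Φ = 0.13.

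| h at Erasmus MC | p₂ | Pooled RR | P(sig. for TIM), n = 263 |
|---|---|---|---|
| 10% | 0.284 | 0.95 | 6% |
| 20% | 0.267 | 0.89 | 13% |
| 50% | 0.218 | 0.73 | 57% |

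The nominal chance in that direction is 2.5%. Because the endpoint is per patient, h counts only patients in whom every error is hidden.

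**The case against.** The case on the other side has real force.

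- **The CPOE/CDS wording is ambiguous.** It could partly mean pre-ICU ward orders, which the Medication data section records as a separate item. That section, however, says pre-ICU where it means it, and the gold-standard definition does not. The ambiguity needs resolving either way.
- **The full chain is not stated.** The post-phase text names no compiler for the BPML-GW24, and the BPMDL-ICU is not listed as a source. That the TIM pharmacist builds the reference from their own entry is a possibility the article leaves open, not a fact it reports. The condensed article may also omit procedural detail, and the study-procedure figure is not shown.
- **Other sources can expose errors.** The BPMH and the ICU record remain, the ICU doctor approves the discharge list and the ward doctor authorizes it. Each BPML-GW24 drug is checked for whether it was prescribed, so omissions can still surface. This safeguard is partial: the BPMH also feeds the BPMDL-ICU, TIM places the BPMH in the PDMS or HIS, and the ward doctor is interviewed only when needed.
- **Pre-filling a correct list is the intervention working.** That stands. Bias arises only where the list is wrong and the reference accepts it.
- **The direction could reverse.** Without a BPMDL-ICU, a wrong pre-phase order is easier to accept as intended. Recorded restart, stop and continue decisions make post-phase deviations easier to see.
- **Some use of the chart is legitimate.** Appropriate new ward orders would otherwise count as false discrepancies.

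A reader might infer that errors are in fact hidden in TIM's favour across the whole post phase. Hiding 20% of affected patients at both sites would give RR 0.80 and a 34% chance of a false significant result. The documents do not support that reading: inpatient pre-registration occurs at one site only, and a pooled 20% loss would need 0.20/0.545 = 37% of affected Erasmus MC patients hidden.

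**Conclusion.** The point holds in limited form. It is established from the text that the discharge reference, as defined, is not independent of the chart it tests, in both phases, and that pharmacist pre-registration at Erasmus MC is a post-phase-only feature of that chart. Together these create a credible risk of differential under-detection in a primary outcome. It is not established that such under-detection will occur, that it must favour TIM, or how large it would be.

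The false-positive range of about 6% to 57% rests on assumed masking of 10% to 50% at one site, no true effect and perfect pre-phase detection. It shows sensitivity and is not an estimate. The planned analysis by site could show a difference between hospitals but could not separate this bias from a true site-specific effect. The definition should be fixed. The flaw does not by itself invalidate the design, and the sample-size inputs do not change.

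**What to change.** Amend the discharge gold-standard definition, identically for both phases:

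1. Compile the BPML-GW24 from the BPMH, the ICU PDMS/HIS record and, if CPOE/CDS data are used, orders explicitly labelled as pre-ICU. Do not copy the BPMDL-ICU.
2. Record a completion date and time in the CRF before the post-discharge chart is opened.
3. Compare the locked list with the chart. Only then use the chart, the notes or the ward doctor, and only to classify each difference, including new ward orders, as intentional or not. State this rule for discharge and apply it in both phases; the written rule under Outcome measures is worded for admission.
4. Where staffing allows, have the list compiled by whichever of the two existing pharmacists did not prepare that patient's BPMDL-ICU. Locking the list does not stop one person repeating the same misjudgement from the same sources.

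The cost is a changed order of work, one CRF timestamp and more discrepancies to classify. Step 4 is conditional so that no new post is needed. The change must precede data collection, because a reference compiled with the chart in view cannot be made independent later.

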### Collection of medication lists

#### Pre-intervention phase

For each included patient discharged from the ICU for at least 24 h, a pharmacist generates a BPMH and a BPML-GW-24 in order to trace medication transfer errors.

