### Study population

All patients admitted to the ICU during the study period are eligible to participate in this study if they use at least one drug at home and if the ICU length of stay exceeds 24 h. An ICU discharge and readmission within 24 h is counted as one inclusion. Patients who die during the ICU stay are included in the admission part of the study. Readmissions to the ICU are also included.

Exclusion criteria are transfer to another hospital, both admission and discharge within the same weekend (Friday 17:00 until Monday 8:30) and patient’s inability to be counseled in Dutch or English.

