### Data analysis

#### Sample size

The primary outcome of this study is the proportion of patients with one or more transfer errors at admission to the ICU and at discharge from the ICU.

Based on literature the expected proportion of patients with medication errors due to transfer between wards within one hospital is 62% [18]. Based on a conservative interpretation of this study, it was estimated that this proportion is 30% in our study. With an estimated 50% reduction of errors due to the intervention, an alpha of 0.05 and a power of 0.80 the calculated sample size is 133. This sample size is based on patients being alive at discharge for both the pre-intervention as the post-intervention phase.

With an estimated mortality of 35%, in each measurement phase 205 patients should be included. Based on 1500 (Haga Teaching Hospital) and 1800 (Erasmus MC) admissions a year, an estimated loss of 30% due to the ICU stay less than 24 h and another 35% loss due to weekend ICU stay, we estimate a study period of 7 weeks for Erasmus MC and 8 weeks for Haga. To be on the safe side and to measure during a robust intervention period, we will double the number of calculated weeks. Therefore a pre- and post-intervention period of 14 weeks is chosen.

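### The population rule and the pre-phase collection rule conflict on whether patients who die in the ICU contribute to the admission outcome

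*Protocol article*

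**What the plan says.** Four parts of the protocol article bear on who has an admission outcome.

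- **Study population:** "Patients who die during the ICU stay are included in the admission part of the study". No phase is named.
- **Sample size:** the base number refers to survivors ("This sample size is based on patients being alive at discharge for both the pre-intervention as the post-intervention phase") and is then raised for deaths: "With an estimated mortality of 35%, in each measurement phase 205 patients should be included". Deaths are thus counted as inclusions in both phases.
- **Collection of medication lists:** in the pre-intervention phase, "For each included patient discharged from the ICU for at least 24 h, a pharmacist generates a BPMH and a BPML-GW-24". In the post-intervention phase, "The pharmacist generates a BPMH for patients newly admitted to the ICU", and the discharge lists are made later as separate steps.
- **Outcome measures:** "An MTE at admission is defined as an unintentional discrepancy between BPMH and medication prescribed within 24 h after admission to the ICU". Without a BPMH this primary outcome cannot be scored.

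**The concern.** In the pre-phase the admission list and the ward list share one trigger: the patient has been out of the ICU for at least 24 h. A patient who died in the ICU never meets it. In the post-phase the admission list is triggered by admission, so it exists whether or not the patient later dies. No other sentence in the article says how or when a BPMH is made for a pre-phase patient who dies.

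At stake is the comparability of the two groups for one of the two primary outcomes. If the rule is followed as written, a subgroup present after the intervention is absent before it. The planned logistic regression could absorb a difference that runs entirely through measured severity. It cannot estimate anything for a subgroup with no pre-phase members. Lists that were never made cannot be supplied by a later analysis plan.

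**Working it through.** **1. The plan's own figures.** Inputs from Sample size: "it was estimated that this proportion is 30% in our study"; "With an estimated 50% reduction of errors due to the intervention", so 0.30 falls to 0.15; alpha 0.05 (taken as two-sided, since sidedness is not stated); power 0.80. The mean proportion is 0.225.

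- Without continuity correction: n = [1.96 × √(2 × 0.225 × 0.775) + 0.8416 × √(0.30 × 0.70 + 0.15 × 0.85)]² / 0.15² = (1.1575 + 0.4889)² / 0.0225 = 120.5, so 121 per phase.
- With continuity correction: n = (120.5 / 4) × [1 + √(1 + 4 / (120.5 × 0.15))]² = 133.5, or 134 rounded up, against 133 stated. This agrees to rounding.
- Raised for deaths: 133 / (1 − 0.35) = 204.6, so 205, as stated.

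**2. Who has an admission outcome under each rule.**

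| Rule followed | Pre-phase | Post-phase |
|---|---|---|
| Study population | survivors and deaths, 205 | survivors and deaths, 205 |
| Collection of medication lists, read literally | survivors only, about 133 | survivors and deaths, 205 |

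Deaths in the post-phase: 0.35 × 205 = 71.75, about 72.

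**3. Relative risk with no programme effect, under the literal rule.** Let s be the MTE risk in survivors, d the risk in patients who die, and m the share of deaths in the post-phase group. Then

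RR = [(1 − m) × s + m × d] / s.

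Take s = 0.30 and m = 0.35, both planning figures in the article (0.30 is used here for survivors). The article gives no value for d, so it is an assumption and is varied.

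- d = 0.15: (0.195 + 0.0525) / 0.30 = 0.2475 / 0.30 = 0.825, about 0.83
- d = 0.30: 0.30 / 0.30 = 1.00, no bias
- d = 0.45: (0.195 + 0.1575) / 0.30 = 0.3525 / 0.30 = 1.175, about 1.18

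With m = 0.10 in place of 0.35, the same range of d gives (0.27 + 0.015) / 0.30 = 0.95 to (0.27 + 0.045) / 0.30 = 1.05.

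**4. Effect on the test.** Take 133 against 205 and a two-sided 5% test.

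- d = 0.15: the standard error is √(0.30 × 0.70 / 133 + 0.2475 × 0.7525 / 205) = 0.0499. The standardised difference is −0.0525 / 0.0499 = −1.05. The null is rejected about 18% of the time.
- d = 0.45: the corresponding figure is about 17%.
- d = 0.30: it is the nominal 5%.

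**5. Power.** For 0.30 against 0.15, without continuity correction, power is about 0.96 at 205 against 205, 0.90 at 133 against 205, and 0.84 at 133 against 133. The literal rule does not leave the admission outcome underpowered.

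**The case against.** The strongest reply is that the article states its intention elsewhere. The population rule covers deaths without a phase limit, and the sample size counts them in each phase. The pre-phase sentence is a condensed account of logistics. It has to name discharged patients because a general ward list cannot exist for anyone else, and it does not say that patients who die get no BPMH. The study flow chart and the figure of pre- and post-intervention procedures are not visible here and may show how deaths are handled. The article also condenses a fuller protocol.

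Much of this stands. A reader might infer that the admission comparison is certain to be survivors against survivors plus deaths, or that pre-phase deaths were left out by choice. The documents support neither inference, and the population rule points the other way. A reader might also infer a loss of power, and the figures above rule that out.

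The size of any bias is open as well. The risks assumed for patients who die have no source in the article, 35% is a planning figure, and even the illustrative extremes lie far from the planned relative risk of 0.5.

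What does not fall away is the missing procedure. An intention to include deaths does not tell pharmacists to make a pre-phase BPMH for them, and the one stated trigger excludes them.

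**Conclusion.** The point holds as an internal contradiction on a primary outcome. The population rule and the sample size include ICU deaths in both phases; the pre-phase collection rule, as written, does not reach them, while the post-phase rule does. If the collection rule is followed literally, about 35% of post-phase admission outcomes would have no pre-phase counterpart.

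The direction and size of the resulting bias cannot be determined from the article. The range of 0.83 to 1.18 is an illustration. It rests on a 30% risk in survivors, 35% mortality, no programme effect, and an assumed 15% to 45% risk in patients who die. It shrinks with lower mortality and vanishes if the two risks are equal. The passages still need to be reconciled, because one stated procedure yields non-comparable groups and the correction is cheap.

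**What to change.** Define the admission analysis set identically in both phases, and bring Study population and Collection of medication lists into line with it. Two routes are open.

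- **Include deaths in both phases.** State under the pre-intervention phase that the BPMH and admission MTEs are determined for every included patient, including those who die in the ICU. Add a sensitivity analysis in patients discharged alive. The cost is extra record-based work. The gold standard calls for an interview with the patient or a relative, so a BPMH made after death may be less well verified and could detect errors differently; the sensitivity analysis addresses this.
- **Restrict to patients discharged alive in both phases.** Amend Study population, make this the primary admission comparison, and report post-phase deaths separately. Death during the ICU stay is already a listed item under Patient data, so no new data are needed. If the condition of 24 h out of the ICU is kept, apply it in both phases. The cost is an admission result that speaks only to ICU survivors.

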#### Post-intervention phase

The pharmacist generates a BPMH for patients newly admitted to the ICU and the Best Possible ICU Medication Discharge List (BPMDL-ICU) for patients planned to be discharged. One day past ICU discharge, a medication chart of current medication in the CPOE/CDS will be printed and a BPML-GW24 will be compiled.

### Outcome measures

Figure 1 presents a summary of outcome measures.

The primary outcome measures of this study are the proportion of patients with one or more MTEs at admission to the ICU and the proportion of patients with one or more MTEs after discharge from the ICU.

An MTE at admission is defined as an unintentional discrepancy between BPMH and medication prescribed within 24 h after admission to the ICU.

An MTE at discharge is defined as an unintentional discrepancy between the BPML-GW24 and the medication chart of the patient within 24 h after discharge.

Whether a discrepancy at admission is unintentional or not is based on information documented in the PDMS, the ICU standards of care and the ICU pharmacist’s interpretation of the situation (see Fig. 4 for the assessment of unintended medication discrepancies).

